## Abstract

**Introduction::**

Polymyalgia rheumatica (PMR) and giant cell arteritis (GCA) are common inflammatory conditions. The diagnosis of PMR/GCA poses many challenges since there are no specific diagnostic tests. Recent literature emphasizes the ability of 18F-fluorodeoxyglucose positron emission tomography/computed tomography (18F-FDG PET/CT) to assess global disease activity in inflammatory diseases. 18F-FDG PET/CT may lead to the diagnosis at an earlier stage than conventional imaging and may also assess response to therapy. With respect to the management of PMR/GCA, there are 3 significant areas of concern as follows: vasculitis process/vascular stiffness, malignancy, and osteoporosis.

**Methods and analysis::**

All patients with suspected PMR/GCR referred to the Rheumatology section of Medicine Department at Svendborg Hospital, Denmark. The 4 separate studies in the current protocol focus on: the association of clinical picture of PMR/GCA with PET findings; the validity of 18F-FDG PET/CT scan for diagnosis of PMR/GCA compared with temporal artery biopsy; the prevalence of newly diagnosed malignancies in patients with PMR/GCA, or PMR-like syndrome, with the focus on diagnostic accuracy of 18F-FDG PET/CT scan compared with conventional workup (ie, chest X-ray/abdominal ultrasound); and the impact of disease process, and also steroid treatment on bone mineral density, body composition, and vasculitis/vascular stiffness in PMR/GCA patients.

**Ethics and dissemination::**

The study has been approved by the Regional Ethics Committee of the Region of Southern Denmark (identification number: S-20160098) and Danish Data Protection Agency (J.nr 16/40522). Results of the study will be disseminated via publications in peer-reviewed journals, and presentation at national and international conferences.

## Introduction

1

Polymyalgia rheumatica (PMR) is the most common inflammatory rheumatic disease that affects individuals over the age of 50 years. The typical symptoms of PMR are bilateral aching and stiffness in selected muscle groups, predominantly in the neck, shoulders, upper arms, and pelvic girdle that are most pronounced in the morning and improve with physical activity.^[1–3]^ Giant cell arteritis (GCA) is an inflammatory vasculopathy that typically involves medium and large arteries.^[4]^ Though involvement of the extracranial branches of the carotid artery can be identified in the classic cranial GCA, GCA may also involve aorta and its major branches, predominantly branches of the proximal aorta, that is, subclavian, axillary proximal brachial arteries, representing a subset of patients with large-vessel GCA (LV-GCA).^[4,5]^ Vasculitis, if untreated, can result in ischemic complications, such as ischemic optic neuropathy, which is responsible for vision loss in 10% to 15% of patients. Whereas the etiology of PMR/GCA is still unknown, genetic and environmental factors may play roles in the development of PMR/GCA. GCA and PMR share many pathogenetic and epidemiological features, and are frequently thought to represent different spectrums of the same clinical entity. Despite the high association between PMR and GCA, it is essential to differentiate these 2 conditions due to different steroid treatment regimes. Corticosteroids are considered the treatment of choice for PMR/GCA, with higher doses required for GCA.^[1–3]^ PMR/GCA is generally not associated with reduced longevity; however, patients with aortic aneurysm/dissection have higher rates of mortality.^[6]^ Additionally, patients are at risk of different comorbidities, both due to the disease characteristic itself and also due to treatment side effects.

Accurate diagnosis of PMR/GCA can be challenging since various diseases mimic these conditions and there are no specific diagnostic tests. PMR is a clinical diagnosis. Careful clinical evaluation and exclusion of several mimics of PMR/GCA can support the diagnosis.^[1–3]^ In cases of suspected GCA, temporal artery biopsy (TAB) should be performed to confirm the diagnosis. However, it is invasive, it can be false-negative in a proportion of patients, and it does not delineate the extracranial component of the disease.^[7,8]^ Laboratory findings are nonspecific in PMR/GCA. Marked elevations in erythrocyte sedimentation rate (ESR) and C-reactive protein (CRP) are frequently seen in PMR/GCA. Thrombocytosis, anemia, and increased alkaline phosphatase may also be presented.^[1,3]^ Different imaging modalities, for example, ultrasonography (US), magnetic resonance imaging, and angiography, are helpful in the diagnosis of PMR/GCA; however, use of these modalities may be limited due to long assessment time for wide vascular assessment, interobserver variation, invasiveness, diminished sensitivity, specificity, and so on.^[9–11]^ There have been several proposed diagnostic criteria for PMR.^[12–15]^ The core components included in these diagnostic criteria were as follows: an age cut-off point, bilateral shoulder or hip pain, morning stiffness, elevated ESR, elevated CRP, rapid steroid response, and disease duration. In 2012, the provisional classification criteria for PMR has been published by European League Against Rheumatism (EULAR) and American College of Rheumatology (ACR).^[10]^ However, it is worth mentioning that these are classification criteria and are designed to differentiate PMR from other diseases that mimic PMR and are not useful to make the diagnosis. Furthermore, the specificity of the 2012 provisional classification criteria for PMR seems to be not sufficient, despite high sensitivity.^[16]^

Positron emission tomography/computed tomography (PET/CT) is a whole-body scan combining molecular and structural imaging in a single examination. The principle is tomographic detection of radiation from intravenously administered radio-labeled tracers targeting disease processes on a cellular or molecular level. Due to its high sensitivity and an inborn ability for quantification, PET can detect diseases at their very early stage and grade their degree of activity.^[17,18]^ The most versatile and widely used tracer, 18F-fluorodeoxyglucose (FDG), is a glucose analog depicting local hypermetabolism (ie, inflammation or cancer). In the clinic, it has mainly been used to detect focal hypermetabolism due to cancer, and the impact in the oncologic domain has been huge as PET/CT appears to cause a change in management in as many as every third patient.^[19]^ However, FDG is nonspecific for cancer as inflammatory lesions also show increased FDG uptake. This was until recently seen as a downside resulting in “false-positive” findings in oncology, but is now considered a great asset, since this allows for detection and characterization of inflammatory processes in many settings. 18F-FDG PET/CT is being investigated clinically in a multitude of inflammatory disorders. High sensitivity, high target-to-background contrast, accurate anatomical localization of sites of inflammation, and an absolute quantification potential may all lead to early assessment of disease processes and their extent.^[20]^

With regard to vasculitis, recent literature emphasizes the ability of 18F-FDG PET/CT to assess inflammation in the vessel walls, whereas FDG uptake patterns in PMR are not yet firmly established. It may locate disease at an earlier stage than conventional imaging and assess response to therapy. Response assessment is based on changes in glucose metabolism from baseline to post-treatment follow-up, and the rates of change are different in responders and nonresponders.^[21]^ Besides locating focal disease, 18F-FDG PET/CT may also assess disease activity more globally, which may be especially interesting in systemic inflammatory diseases. Thus, this research protocol will also incorporate assessment of global disease assessment (ie, “global disease burden”), a novel approach to quantifying disease. By way of novel software-based quantitative methods, the radioactivity throughout the body can be quantified, summed, and presented as 1 single number, the systemic inflammatory activity or “global disease burden.” The method is new and not yet firmly established, but it holds significant promise, especially for response assessment in systemic inflammatory diseases.^[22,23]^

Therefore, we plan to conduct a prospective study to explore the role of 18F-FDG PET/CT scan in the management of PMR/GCA. In addition, 3 significant areas of concern in the management of PMR/GCA including: osteoporosis due to steroid treatment or disease characteristics itself, malignancy, and vasculitis/vascular stiffness will be investigated during the project. This research protocol consists of four separate studies designed to achieve below mentioned objectives that are discussed individually later in the text (Fig. 1).

**Figure 1 F1:**
[figure not shown]
Summary of study I to IV. GCA = giant cell arteritis, PMR = polymyalgia rheumatica, TAB = temporal artery biopsy.

## Objectives

2

### Primary

2.1

The primary objective of this study is to explore the association of 18F-FDG PET/CT findings and uptake patterns (PET positivity/negativity) and the clinical picture of PMR/GCA.

### Secondary

2.2

1.To investigate the validity of 18F-FDG PET/CT scan for diagnosis of PMR/GCA compared with temporal artery biopsy.2.To compare the efficacy of nationally recommended conventional diagnostic workup to detect occult malignancies in the setting of PMR/GCA (ie, chest X-ray [CXR] plus abdominal US) with 18F-FDG PET/CT at diagnosis and during the first year after diagnosis.3.To evaluate the influence of inflammation on regional and total bone mineral density (BMD) and body composition, and also vasculitis/arterial stiffness of aorta at diagnosis of PMR and within a year after treatment initiation with prednisolone.

### Patient research partners (PRPs)

2.3

Active collaboration between patients and researchers is relatively a new concept in the research field which is a useful tool to capture the patient perspective. By means of this, better representation of patients’ needs and uncertainties can be secured. It additionally avoids potential mismatch between patients’ preferences and researchers objectives. EULAR has introduced the recommendation for the inclusion of patient representatives in scientific projects.^[24]^ This research protocol will also adhere to the EULAR recommendation. Thus, 2 PRPs (co-authors [name] and [name]) were invited to help us design the study. The involvement of PRPs with respect to 8 significant aspects of EULAR recommendation is depicted in Table 1.

**Table 1 T1:**
[figure not shown]
Patient research partners (PRPs).

## Methods and analysis

3

### Study setting

3.1

The current study will be performed at the Department of Rheumatology, Svendborg Hospital, Odense University Hospital, Svendborg, Denmark. The Rheumatology Department of Svendborg Hospital has the capacity of enrolling PMR/GCA patients that are required for this study, since all patients from all over Funen County with suspicious PMR/GCA will be referred to the Diagnostic Center for primary investigation at Svendborg Hospital. After confirmed PMR/GCA condition the patients will be referred to the local Rheumatology department for study inclusion.

All parts of the project will take place at Svendborg Hospital, except the 18F-FDG PET/CT scans and bone densitometry, which will be undertaken at the Department of Nuclear Medicine and Department of Endocrinology, respectively, Odense University Hospital, Odense, Denmark. The 18F-FDG PET/CT will be performed as routine whole-body scan (from vertex of the skull to the knees) 60 minutes after injection of a weight-adjusted dose of FDG according to the guidelines from the European Association of Nuclear Medicine.^[25]^ The CT-part is a low-dose CT without contrast enhancement.

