### Participants

3.3

All new patients with clinical suspicion of PMR/GCA will be offered to be included in the study. At least 5 (A–E) components of the PMR diagnostic criteria, including: age ≥50 years, bilateral shoulder or hip pain, morning stiffness lasting >45 minutes, elevated ESR, elevated CRP, disease duration >2 weeks, should be met to suspect PMR.^[3]^ For GCA, the following criteria must be considered: age >50 years, ESR/CRP >50, and also at least 2 symptoms related to vasculitis (scalp tenderness, vision disturbances, headache [new or changed], jaw claudication, tenderness of the temporal arteria) if patients do not simultaneously have PMR. If the patient is suspected for PMR, 1 cranial symptom is enough to suspect GCA. Besides, clinical suspicion of LV-GCA, that is, upper-extremity claudication, upper-extremity blood pressure discrepancies, and abnormal radial pulse, will be registered.

The exclusion criteria (study I–IV) are as follows:1.Patients with dementia or inability to communicate in Danish2.Infections or malignancy when prednisolone is permanently unsuitable3.Contraindication to imaging studies (pregnancy and blood sugar [BS] >8 mmol/L after 6 hours fasting)4.Initiation of steroid treatment before the 18F-FDG PET/CT scan5.Inability to provide informed consent

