This study is a blinded prospective investigation. At diagnosis all patients undergo a CXR and abdominal US, as recommended by the Danish Rheumatology Association. The 18F-FDG PET/CT scan in every included patient (as described in study I) will be assessed with regards to malignancies before results are blinded to the clinicians for 1 year. This assessment will be blinded to other clinical and imaging results and findings on 18F-FDG PET/CT scan will be compared with CXR/abdominal US results to establish the relative diagnostic accuracy of these 2 strategies for malignant and infectious diseases in PMR/GCA patients. In case of detecting or developing any kinds of malignant disease during the study, the patients will be referred to the relevant department for further work-up and treatment. This will not be a reason for exclusion, but depends on individual assessment of the patient. 18F-FDG PET/CT scan may also be repeated for individual patient if necessary.

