### Recruitment

3.10

All patients with the suspicion of PMR/GCR are referred to the Diagnostic Center, Svendborg Hospital. After primary investigation and evaluation, the eligible patients will be referred to the Rheumatology Department of Svendborg Hospital for formal enrolment in the study. Patients will be informed orally and written about the voluntary nature of the participation and project objectives, content, risks, and benefits. A deliberation time of 24 hours will be considered from submission of the oral and written information to obtain informed consent. Consent statement will be reviewed, signed, and dated by the patient and handed over to the department. The patient receives a signed copy of the consent form and be informed of that he/she can withdraw from the study at any time without any reason nor consequences. A scanned copy of patient consent will be added to the patient electronic hospital record, and one additional copy will be stored in a locked room at the department.

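### Section 3.1 admits patients only after PMR/GCA is confirmed, while the abstract and 3.3 admit on suspicion; the confirmed route would divert mimics and could bias Study III towards PET/CT

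*Protocol article*

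**What the plan says.** The protocol article describes entry in four places.

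- **Section 3.1, Study setting:** "After confirmed PMR/GCA condition the patients will be referred to the local Rheumatology department for study inclusion".
- **Section 3.3, Participants:** "All new patients with clinical suspicion of PMR/GCA will be offered to be included in the study". The criteria that follow are thresholds for suspecting PMR or GCA, not for confirming either.
- **Abstract, Methods and analysis:** "All patients with suspected PMR/GCR referred to the Rheumatology section of Medicine Department at Svendborg Hospital, Denmark".
- **Section 3.10, Recruitment:** "After primary investigation and evaluation, the eligible patients will be referred to the Rheumatology Department of Svendborg Hospital for formal enrolment in the study". Its opening sentence concerns patients under suspicion, and it does not use the word confirmed.

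Three further statements bear on Study III. Its title (3.4.3) covers PMR-like syndromes as well as PMR and GCA. On the comparator, 3.4.3 says: "At diagnosis all patients undergo a CXR and abdominal US, as recommended by the Danish Rheumatology Association". It does not say whether this happens before or after inclusion.

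On malignancy, the second exclusion criterion for all four studies reads "Infections or malignancy when prednisolone is permanently unsuitable". For malignancy detected or developing during the study, 3.4.3 says "This will not be a reason for exclusion, but depends on individual assessment of the patient".

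**The concern.** Confirmed and suspected PMR/GCA are two different study populations, and the text states both. Study III is the study most exposed. It aims to estimate how often malignancy is newly found in this clinical setting and to compare PET/CT with CXR/US as ways of finding it. Section 3.4.3 itself notes that malignancies can produce PMR-like symptoms, and the Introduction says that diagnosis rests on excluding mimics. A patient whose apparent PMR turns out to be cancer is therefore the patient a confirmed-only entry rule would send elsewhere.

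A second risk is conditional. Section 2.2 describes CXR plus abdominal ultrasound as the nationally recommended conventional work-up, and 3.1 and 3.10 place a primary investigation before referral for inclusion. If CXR/US belongs to that investigation and a cancer found there prevents confirmation, one of the two strategies under comparison has filtered the sample before the comparison starts.

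**Working it through.** **1. Which reading do the other passages support?**

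| Place | Entry condition |
|---|---|
| Abstract | Suspected |
| 3.1 | Confirmed |
| 3.3 | Suspected, with criteria for suspicion |
| 3.10 | Eligible after primary investigation; neither word decides |
| 3.4.3, title | Includes PMR-like syndromes, which fits suspected entry only |

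Section 3.1 stands alone, but it is explicit and describes the actual referral route.

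**2. The plan's own Study III figure.** Inputs from section 3.12: one-sided 5%, power 80%, discordant proportions p10 = 0.15 (PET only) and p01 = 0 (CXR/US only), N = 80. With psi = p10 + p01 and d = p10 − p01,

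n = (1.645·√psi + 0.842·√(psi − d²))² / d² = (1.645·√0.15 + 0.842·√0.1275)² / 0.0225 = 39.07, so 40 patients.

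At N = 80 the power is 97.6% (asymptotic) or 99.5% (exact). The statement that 80 is sufficient therefore holds on its own assumptions, although 80 is not the minimum.

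**3. Why the CXR/US-only cell matters.** Keep p10 = 0.15 and N = 80, and vary p01. These values are assumptions; the protocol gives only 0%.

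| p01 | Patients of 80 | Asymptotic power | Exact power |
|---|---|---|---|
| 0 | 0 | 97.6% | 99.5% |
| 1.25% | 1 | 93.3% | 93.4% |
| 2.5% | 2 | 85.9% | 83.2% |
| 3.75% | 3 | 75.9% | 70.5% |
| 5% | 4 | 64.2% | 57.0% |

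If every cancer found by CXR/US were removed before entry, p01 would be zero by construction, whatever its true value.

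**4. Direction of the selection effect.** Let a be cancers found by both methods, b by PET only and c by CXR/US only. Full removal of cancers found by CXR/US deletes a and c. The exact one-sided McNemar P is P(X ≥ b) for X ~ Bin(b + c, ½), so it depends on b and c but not on a. The counts below are assumed and show direction only. Shares are out of all cancers found by either method.

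| a / b / c | PET share, all kept | CXR/US share, all kept | P, all kept | P after removal |
|---|---|---|---|---|
| 2 / 4 / 0 | 6/6 = 100% | 2/6 = 33% | 0.063 | 0.063 |
| 4 / 4 / 1 | 8/9 = 89% | 5/9 = 56% | 0.188 | 0.063 |
| 4 / 8 / 2 | 12/14 = 86% | 6/14 = 43% | 0.055 | 0.004 |

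After full removal, PET finds 100% and CXR/US 0% in every row. In the last row the cancers counted fall from 14 to 8. Losing cancers found by both methods lowers prevalence and CXR/US detection but leaves the test unchanged (first row). Losing CXR/US-only cancers moves the test towards PET/CT (second and third rows).

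**The case against.** The strongest reply is that 3.1 is one loosely worded sentence and the rest of the protocol points to suspected entry. PMR has no specific test, and temporal artery biopsy (TAB), which confirms GCA, is itself a study procedure. Section 3.3 is where eligibility is defined. This is a fair guide to what was probably meant. It does not remove the contradiction, because 3.1 describes how patients reach the study.

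The reply also rightly limits several stronger readings that a reader might infer.

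- **That cancers found by CXR/US are certainly lost.** The protocol does not place CXR/US before inclusion. The second exclusion criterion reaches only malignancy that makes prednisolone permanently unsuitable. The loss is possible, not stated.
- **That the exclusion and 3.4.3 contradict each other.** One can be read as an entry rule and the other as a rule for malignancy arising during the study. They are compatible on that reading, but the boundary between them is not drawn.
- **That the assumed 0% for CXR/US-only detection is an enrolment artefact.** It is a sample-size assumption, not a result.
- **That one restored cancer decides the test.** With assumed counts, 5 v 0 gives P = 0.031 and 5 v 1 gives 0.109. But 4 v 0 is already 0.063, and 7 v 1 is still 0.035. The protocol gives no expected count from which to choose among these.
- **That Study II cannot estimate specificity.** Study II plans proportions of agreement between PET/CT and TAB (3.8 and 3.12). Patients with confirmed PMR or GCA can be TAB-negative, so negative agreement remains estimable under either entry rule. Specificity against a final clinical diagnosis would lack non-cases in a confirmed-only sample, but it is not a planned analysis.

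Finally, Study III is secondary, and 3.9 calls the secondary objectives hypothesis generating. That limits the consequence. It does not make a filtered comparison interpretable.

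**Conclusion.** The concern stands in a limited form. Section 3.1 conflicts with the abstract, with 3.3 and with the population named in the title of Study III, and 3.10 does not resolve it. Followed as written, 3.1 would divert mimics before entry.

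The further bias, in which CXR/US detection and observed prevalence are understated and the McNemar comparison favours PET/CT, rests on two conditions that the protocol leaves open: that CXR/US precedes inclusion, and that a cancer found there blocks entry. The test itself shifts only if CXR/US-only cancers are lost. The direction is clear under those conditions, but the size cannot be derived from the document; every count in the illustrations is an assumption.

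Nothing here shows an effect on the primary objective, and the planned agreement analysis of Study II is not undermined. The contradiction should still be settled, because patients turned away before enrolment cannot be recovered at analysis.

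**What to change.** 1. Change 3.1, and clarify 3.10, so that the single entry point is clinical suspicion of PMR/GCA as defined in 3.3.
2. State when CXR/US takes place relative to enrolment, and enrol patients before its result is used to decide inclusion.
3. Keep every scanned patient in the Study III denominator, including those with malignancy or another final diagnosis.
4. Report the flow from referral to enrolment, with reasons for non-entry and a count of malignancies found before entry and by which method.
5. Reconcile the second exclusion criterion in 3.3 with the statement on malignancy in 3.4.3, so that it is clear where each applies. Which rule should govern is for the investigators.

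The cost is an amendment to the eligibility and recruitment wording, plus a screening log. Some of the 80 places will go to patients who prove not to have PMR/GCA, so Studies I and IV will analyse slightly fewer.
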